### Sample Size Estimation

With the total teacher population in Lusaka, Livingstone, Kasama, and Solwezi of about 30,561 [66], using a web-based script [77], it is projected that the sample size needed for our prevalence estimates with 95% confidence and a 3% margin of error for moderate to high stress, burnout, moderate to high anxiety, moderate to high depression, and low resilience among teachers in Livingstone, Lusaka, Kasama, and Solwezi will be 993. Based on the maximum survey completion rate attained for the Text4Hope and Text4Mood programs in Alberta of 20% [50,78,79], to achieve an estimated 993 completed surveys at baseline, it is planned to enroll at least 4965 teachers in the Wellness4Teachers email supportive and mental health literacy messaging program within 12 months.

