### Study Setting

The study will occur in Zambia. Zambia is an eastern, sub-Saharan African country with an estimated 2021 population of 18,920,657 and nearly half of the population under the age of 15 years, with almost equal proportions of males and females (49.5% and 50.5%, respectively) [65]. Zambia covers about 290,587 square miles (743,390 km^2^), and the population’s median age is only 16.8 years [65,66]. The country is prone to natural and man-made disasters such as floods, droughts, mine accidents, and deforestation [49]. War and other political uncertainty in surrounding states result in a refugee influx. The study will focus on 4 main cities in Zambia: Livingstone, Lusaka, Kasama, and Solwezi. Livingstone is a capital city in the southern part of the country, with a land area of 85,283 km^2^ and a population of 1,799,885 in 2014. There were about 1241 basic schools in 2012 and 45 high schools in 2004. In 2014, there were 6158 teachers in school grades 1-9, and 1027 in high school [67].

Lusaka is the capital of Zambia and one of the 20 cities in Zambia, with a total land area of 375 km^2^ with an approximate population of 3,042,000 in 2022, a 4.68% increase from 2021 [68]. There were 111 secondary schools and 758 primary schools in Lusaka in 2017 [66], and about 10,822 primary school teachers and 3383 secondary school teachers in Lusaka in 2016 [66]. There are several rural cities in Zambia, including Kasama (Northern Province) and Solwezi (North Western Province). Kasama had a land area of 77,650 km^2^ and a population of 1,264,212 in 2014. There were 1208 basic schools and 26 high schools in 2004. In 2004, there were 5169 teachers in all schools, grades 1-9, and 656 teachers in high schools, grades 10-12 [67]. Solwezi has a land area of 125,826,656 km^2^, and a total population of 811,706 was recorded in 2014. Basic schools in 2012 were 747 and 23 high schools in 2004. Teachers in all schools in grades 1-9 were 2837 in 2004, while teachers in high schools in grades 10-12 were 509 the same year [67].

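### At the usual 50% prevalence, 993 completed surveys does not follow from a population of 30,561 (about 1031 would); the effect on precision is small

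*Protocol article*

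**What the plan says.** Sample Size Estimation takes its population from the four study cities: "With the total teacher population in Lusaka, Livingstone, Kasama, and Solwezi of about 30,561". The target is the "sample size needed for our prevalence estimates with 95% confidence and a 3% margin of error", applied to stress, burnout, anxiety, depression and low resilience alike, and the number required "among teachers in Livingstone, Lusaka, Kasama, and Solwezi will be 993". The calculation is attributed to a web-based script. No assumed prevalence is given.

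The section then divides by a 20% survey completion rate, the highest seen in two earlier messaging programmes. So, "to achieve an estimated 993 completed surveys at baseline", "it is planned to enroll at least 4965 teachers".

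The teacher counts behind the population are in Study Setting, city by city. For Lusaka it gives "about 10,822 primary school teachers and 3383 secondary school teachers in Lusaka in 2016"; for Livingstone it says "there were 6158 teachers in school grades 1-9, and 1027 in high school". Kasama has 5169 and 656, and Solwezi 2837 and 509.

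**The concern.** The section names its population, confidence level and margin, so a reader can repeat the calculation. With the prevalence normally used when none is specified, the result is not 993. The number that does give 993 is the teacher count of one of the four cities.

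This is the only sample size justification in the article, and the enrolment target is built directly on it. At stake is whether the published target and the published margin belong to the same population.

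**Working it through.** **Inputs from the article.** Population N = 30,561; 95% confidence (z = 1.96); margin e = 0.03; completion rate 20%. City counts from Study Setting:

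- Livingstone: 6158 + 1027 = 7185
- Lusaka: 10,822 + 3383 = 14,205
- Kasama: 5169 + 656 = 5825
- Solwezi: 2837 + 509 = 3346
- Sum: 7185 + 14,205 + 5825 + 3346 = 30,561, which is the stated population exactly.

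**Assumption.** The prevalence p is not stated. I take p = 0.50, the conservative choice when one sample size must serve five different prevalences, and show a range below.

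**Formula.** n0 = z² p(1 − p)/e², then n = n0/(1 + (n0 − 1)/N).

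n0 = 1.96² × 0.25/0.03² = 1067.1

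**Trying to reproduce 993 at p = 0.50**

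| Population used | N | n |
|---|---|---|
| Four cities (as stated) | 30,561 | 1031.1 |
| Lusaka only | 14,205 | 992.6, rounds to 993 |
| Livingstone only | 7185 | 929 |
| Kasama only | 5825 | 902 |
| Solwezi only | 3346 | 809 |

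The other common form of the correction, n0/(1 + n0/N), also gives 1031.1 for the four cities. Using z = 2 gives 1072, and leaving out the correction gives 1067. At p = 0.50, any population from about 14,182 to 14,389 rounds to 993. Lusaka's count lies in that range; the stated total does not.

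**Could another prevalence explain 993 with N = 30,561?** At p = 0.41, n = 998.8; at p = 0.40, n = 991.2. At p = 0.402, n0 = 3.8416 × 0.402 × 0.598/0.0009 = 1026.1 and n = 1026.1/(1 + 1025.1/30,561) = 992.8, which rounds to 993. So a prevalence of about 40.2% would do it, but the article mentions no such value.

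**Enrolment.** 993/0.20 = 4965, so that step is correct. With 1031 it is 5155 and with 1032 it is 5160, which is 190 to 195 more.

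**Margin actually obtained with 993 completers from 30,561.** Margin = 1.96 √(p(1 − p)/n) × √((N − n)/(N − 1)). At p = 0.50 this is 1.96 × √(0.25/993) × √(29,568/30,560) = 0.0311 × 0.9836 = 0.0306.

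| Prevalence | Margin (percentage points) |
|---|---|
| 50% | 3.06 |
| 45% | 3.04 |
| 42% | 3.02 |
| 40% | 3.00 |
| 38% | 2.97 |
| 33% | 2.88 |

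The margin is symmetric about 50%, so 3% is exceeded only between about 40% and 60%, and by at most 0.06 points.

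**The case against.** The strongest reply is that the mismatch depends on an input the article does not give. The script is not shown, and a prevalence near 40.2% would yield 993 from the stated population. That is arithmetically true, so the finding is conditional on p = 0.50. As an explanation it is weak: the article supports no such value, one tuned prevalence makes little sense for five conditions, and the ordinary default combined with the article's own Lusaka count gives 993.

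A second reply is that the difference hardly matters. Most of this stands. A worst-case 3.06% is still 3% when stated as a whole percentage. The single-study figures quoted in the Background (25.3%, 33.3%, 35.3% and 38%) all lie where the 3% margin is met. The Background also quotes ranges that cross 40% to 60%, such as burnout from 25.12% to 74%, so a marginal miss is possible. Enrolment is set as a minimum, and completion of 1031/4965 = 20.8% instead of 20% would close the gap. Uncertainty about completion is a much larger matter: at an illustrative 15%, 4965 enrolments would return about 745 surveys, and the Limitations section itself expects response below 20%.

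Two stronger readings are tempting. One is that the study will not deliver its stated precision; the margins do not support that. The other is that the authors widened the study from Lusaka to four cities and forgot to recalculate. The exact match points that way. So does the citation: the four-city total is referenced only to the source that Study Setting uses for Lusaka's counts, whereas the other three cities' counts come from a different one. But the article contains no Lusaka-only version and no change history, so this remains an inference.

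**Conclusion.** The inconsistency is real and minor. Assuming 50% prevalence and a finite-population correction, the stated population, confidence and margin require 1031 to 1032 completed surveys, not 993, and 5155 to 5160 enrolments, not 4965. The match with Lusaka's 14,205 teachers makes a carry-over the likeliest explanation, without proving it.

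The loss of precision is at most 0.06 percentage points and arises only for prevalences of about 40% to 60%. It concerns baseline prevalence, which the article lists as a secondary objective; the primary outcomes are changes from baseline, and the section does not size the study for those. The reason to correct it is that a published planning figure cannot be reproduced from its stated inputs under the usual assumption.

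**What to change.** Any one of three changes to Sample Size Estimation resolves it:

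- Keep 993 and 4965, and state the worst-case margin as about 3.1% (3.06%) for a population of 30,561. This needs no extra participants.
- Keep the 3.0% margin, and state 1031 to 1032 completed surveys and 5155 to 5160 enrolments. This adds 38 to 39 surveys and 190 to 195 enrolments.
- If a prevalence other than 50% was used, state it and the reason for it. This also needs no extra participants.

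Whichever is chosen, the section should name the assumed prevalence and say that a finite-population correction was applied, so that the figure can be checked. The cost is one corrected sentence.

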### Outcomes and Measures

Validated screening scales for self-reported symptoms will be used to assess clinical outcomes. These include the Mental Health Literacy Scale [69], the Generalized Anxiety Disorder 7-item (GAD-7) Scale (a GAD-7 score of ≥10 indicates moderate to high anxiety) [70], the Perceived Stress Scale (PSS-10) (a PSS-10 score of ≥10 indicates likely moderate to high stress) [71], the Brief Resilience Scale (BRS; BRS mean scores ranging from 1.00 to 2.99 indicate low resilience, scores from 3.00 to 4.30 suggest normal resilience, and mean scores from 4.31 to 5.00 suggest high resilience) [72,73], and the Patient Health Questionnaire-9 (PHQ-9; a score of ≥10 indicates moderate to high depression) [74]. Burnout will be assessed using the Maslach Burnout Inventory (MBI), specifically the MBI-Educators Survey, for use with educators [75,76]. An exploratory outcome will be to evaluate the acceptance of the Wellness4Teachers program by teachers in Zambia, which can be measured by the proportion of the target population (teachers in Livingstone, Lusaka, Kasama, and Solwezi) who subscribe to the program. Primary outcomes for this study will be changes in mental health literacy and the prevalence of moderate to high stress, burnout, moderate to high anxiety, moderate to high depression, and low resilience from baseline to 6 weeks, 3 months, 6 months, and 12 months among the subscribers of the Wellness4Teachers Zambia program. Secondary outcomes include the mean score on the Mental Health Literacy Scale and the prevalence of moderate to high stress, burnout, moderate to high anxiety, moderate to high depression, and low resilience at baseline in subscribers of the Wellness4Teachers email messaging program. Other secondary outcome measures will include changes in mean scores on the PSS-10, MBI, GAD-7, PHQ-9, and BRS. In addition, sociodemographic factors, work-related factors, and mental health literacy correlate with moderate to high stress, burnout, moderate to high anxiety, moderate to high depression, and low resilience at baseline among subscribers of the Wellness4Teachers program.

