### Statistical Analysis

SPSS (version 25; IBM Corp) [80] will be used to analyze the quantitative data from the surveys. Surveys with more than 50% missing responses will not be included in the data analysis. There will be no missing data imputation, and the analysis of the included survey responses and results will be based on completed survey data. Descriptive statistics for demographic, mental health literacy, clinical, and burnout-related variables will be provided. A 2-tailed *P*≤.05 will be used to determine statistical significance for all analyses, and descriptive characteristics will be presented as percentages and numbers. A chi-square test and logistic regression analysis will be used to separately identify demographic, clinical, and work-related correlates of anxiety, depression, stress, low resilience, and burnout for elementary and high school teachers. Significant and borderline significant variables from the chi-square analysis would be used to develop multivariable binary logistic regression models to predict the adjusted odds of outcomes for the exposure of interest and each potential correlate. The impact of the email supportive messaging program in reducing moderate to high anxiety, moderate to high depression, moderate to high stress, burnout, and improving resilience among subscribers will be evaluated by comparing the mean changes in these parameters from baseline to 6 weeks, 3 months to 6 months, and 12 months using the paired *t* test. To assess the effects of the intervention against a control group, we will choose a defined period of 3 months during the study period (for instance, the beginning of January 2023 to the end of March 2023) and compare the prevalence and mean scores on standardized scales for stress, anxiety, burnout, and depression at 6 weeks for subscribers who have received the daily supportive SMS text messages for 6 weeks (the intervention group) to the baseline prevalence and mean scores on the same scales for new subscribers during the period (the control group).

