### Limitations

Like most studies, this one has some limitations. First, the supportive email messages will be delivered for 12 months, and the outcome measures will be evaluated at 6 weeks, 3 months, 6 months, and 12 months. It is not certain what the effects of the intervention would be if it were extended. It is also unclear if the benefits of the intervention would diminish with the cessation of daily email messages. Second, although standardized, the self-reported scales used to assess mental health variables, such as moderate to high anxiety, are not diagnostic. Third, it is possible that participants’ demographics in the study may not reflect the demographics of the teacher population in Zambia; hence, the study findings may not be generalizable to all teachers in Zambia. In addition, web-based surveys with survey links delivered through SMS text messages usually achieve a response rate of less than 20% [54,78,79,83-86], so it is possible that we may not achieve our desired sample size with an email messaging program. Despite these limitations, this study is the first to assess the prevalence and correlates of stress, burnout, anxiety, and depression among teachers in Zambia using an email messaging program. To our knowledge, this study is also the first worldwide to assess if daily supportive email messages and mental health literacy information delivered by email would effectively reduce the prevalence and severity of psychological symptoms and improve mental health literacy among teachers.

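### The 3-point margin claimed for prevalence among all teachers in the four cities holds for a random sample, not for self-selected subscribers with at most 20% survey completion

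*Protocol article*

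**What the plan says.** Sample Size Estimation starts from a finite population: "With the total teacher population in Lusaka, Livingstone, Kasama, and Solwezi of about 30,561". It then gives "the sample size needed for our prevalence estimates with 95% confidence and a 3% margin of error" for five conditions, ending with "low resilience among teachers in Livingstone, Lusaka, Kasama, and Solwezi will be 993". The population in that sentence is teachers of the four cities. The Abstract (Objective) and Study Objectives, Aims, and Purpose go wider and speak of school teachers in Zambia.

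Outcomes and Measures defines the same quantity differently. There the secondary outcome is prevalence "at baseline in subscribers of the Wellness4Teachers email messaging program".

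Participants' Recruitment and Subscription describes no random draw. A teacher enters by accepting an invitation to subscribe. The completion assumption reads "Based on the maximum survey completion rate attained for the Text4Hope and Text4Mood programs in Alberta of 20" (per cent), and it is used only to raise enrolment from 993 to 4965. The Limitations section adds that surveys of this kind usually fall below 20%, and that participants' demographics "may not reflect the demographics of the teacher population in Zambia".

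Under Statistical Analysis there is no imputation, and "the analysis of the included survey responses and results will be based on completed survey data".

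**The concern.** A margin of error from a single-proportion formula measures one thing: chance variation when every member of the population had a known, equal probability of being drawn. Here a teacher passes two filters, first subscribing and then completing the survey, and neither is under the investigators' control. Both could be related to the outcome. The programme is built to address stress, burnout, anxiety and depression, which are among the conditions being estimated. The Hypothesis section also expects demographic, socioeconomic and organisational factors to be associated with them.

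Two parts of the protocol also disagree about whose prevalence is being estimated. The sample size is justified for teachers, while the outcome is defined for subscribers. Baseline prevalence is a secondary objective, but it is the only one for which a sample size is given. It is to be compared with other jurisdictions, and the Conclusions expect the study to inform policy. A reader who takes 3 points as the accuracy of a figure for the teacher population would be misled about the main source of error.

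**Working it through.** **Inputs from the protocol.** Confidence 95% (z = 1.96), margin e = 3 points, population N = 30,561, n = 993, completion r = 20% at most, enrolment 4965. The assumed prevalence is not stated (the figure was obtained "using a web-based script"), so p = 0.5, the worst case, is an assumption.

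**1. The stated sample size.** With simple random sampling and a finite population correction:

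- n0 = z²p(1 − p)/e² = 1.96² × 0.25/0.03² = 1067.1
- n = n0/[1 + (n0 − 1)/N] = 1067.1/(1 + 1066.1/30,561) = 1031.1, so 1032

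This is not 993. The Lusaka counts alone (10,822 + 3383 = 14,205) give 992.6, which rounds to 993. That discrepancy is a separate matter. What counts here is that the calculation is of the random-sample type. Enrolment reproduces exactly: 993/0.20 = 4965.

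**2. Random-sample margin at n = 993.** 1.96 × √[(0.25/993) × (30,561 − 993)/(30,561 − 1)] = 3.06 points. So even under random sampling the figure for the stated population is about 3.1.

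**3. How selected the respondents are.** Planned subscribers are 4965/30,561 = 16.2% of the stated population, and planned completers are 993/30,561 = 3.2%.

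**4. Non-completion bias among subscribers.** Bias = (1 − r) × (prevalence in completers − prevalence in non-completers). The protocol gives no gap, so the gaps below are assumptions. Coverage is that of a nominal 95% interval of ±3 points, with standard error 3/1.96 = 1.53.

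| Assumed gap (points) | Bias at r = 20% (points) | Coverage |
|---|---|---|
| 2 | 1.6 | about 82% |
| 3.75 | 3.0 | bias equals the margin |
| 5 | 4.0 | about 26% |
| 10 | 8.0 | below 0.1% |

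**5. Measured against all teachers.** If the gap is instead between the 3.2% who complete and all other teachers, the multiplier is 0.968, and a gap of 3.0/0.968 = 3.1 points uses up the margin. Step 4 leaves out the subscription stage, which could add to the bias or partly offset it.

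**6. What weighting could and could not do.** Lusaka is 14,205/30,561 = 46.5% of the stated population. Suppose it supplied 60% to 80% of surveys and prevalence differed by 10 to 20 points between Lusaka and the rest (all assumptions). The composition error would run from (0.60 − 0.465) × 10 = 1.4 points to (0.80 − 0.465) × 20 = 6.7 points. The Kish design effect for two cells, 0.465²/s + 0.535²/(1 − s), is 1.08, 1.26 and 1.70 at Lusaka shares s = 0.6, 0.7 and 0.8. The margin then becomes 3.06 × √1.08 = 3.2 up to 3.06 × √1.70 = 4.0 points.

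These costs are for two cells only. With eight cells (city by school level) and 80% of surveys from Lusaka, about 199 surveys remain for the other three cities. Shared out by the Study Setting counts, Kasama high schools would have 199 × 656/16,356 ≈ 8 and Solwezi high schools 199 × 509/16,356 ≈ 6, too few to carry weights.

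**The case against.** The strongest reply is that the protocol already says this. Limitations concedes that demographics may differ, that findings may not generalise to all teachers in Zambia, and that response may fall short. Outcomes and Measures already uses subscribers as the population. The 3% is a planning figure, and nothing says that results will be published with it. Much of this stands, and it keeps the point to one of wording and labelling. It does not remove the point: the caveat concerns generalising to Zambia, whereas the margin is claimed for the four cities and is left unqualified.

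Three stronger readings are tempting, and the document does not support them.

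- *The plan commits to unweighted estimates.* Statistical Analysis neither mentions nor rules out weights, and the sentence on completed surveys is about imputation. This is a condensed article whose analysis plan is not shown, so silence on weighting is not a fault.
- *The protocol already holds the counts needed to correct the estimate.* Study Setting dates the Lusaka counts to 2016, Livingstone to 2014, and Kasama and Solwezi to 2004. Lusaka is split into primary and secondary, the others into grades 1-9 and high school. The land areas given (85,283 km² for Livingstone against 375 km² for Lusaka) make it doubtful that all counts refer to cities. Weighting to them could add error.
- *Post-stratification would remove the bias.* It would do so only where respondents represent non-respondents within each cell. It would not touch self-selection on unmeasured factors, and it would reduce the bias in step 4 only as far as the weighting cells explain the gap.

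**Conclusion.** The concern holds in limited form. Sample Size Estimation attaches a random-sample margin to all teachers of the four cities, while the design yields responding subscribers, so the stated precision does not apply to the stated population. An assumed completer/non-completer gap of about 3.75 points is enough for non-completion bias alone to equal the 3-point margin. Gaps of 2 and 5 points would cut coverage to about 82% and 26%.

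These sizes illustrate sensitivity. They do not show that any particular bias will occur, because the protocol gives no prevalence for non-completers or non-subscribers. The random-sample figure of 3.06 points rests on p = 0.5. The conclusion about the population does not depend on any of these assumptions.

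**What to change.** 1. In Sample Size Estimation, restate the margin as planning error under simple random sampling, about 3.1 points for 993 completed surveys out of 30,561 at p = 0.5, and say that it excludes selection and non-response error.
2. Align the Abstract (Objective), Study Objectives, Aims, and Purpose, and Sample Size Estimation with Outcomes and Measures. Report and interpret baseline prevalence as *among responding subscribers*.
3. Optionally, add a supplementary sensitivity analysis, only if consistent same-year teacher counts for the four cities are obtained: prevalence post-stratified on a few coarse cells, for example city, with a design-based interval. State that it corrects only measured composition and gives a wider interval. Do not use the Study Setting counts as weights, and do not make this the headline estimate.

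Items 1 and 2 cost a few sentences and need no new data. Item 3 requires counts from outside the document as well as some analysis. Its price in precision depends on the cells: the 3.2 to 4.0 points shown above are for two cells under assumed Lusaka shares, and finer cells could cost more. A larger volunteer sample is no substitute, since it narrows the interval without reducing selection bias.

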### Hypothesis

Based on the greater than 20% reduction in depression symptom scores in the intervention group compared to the control group in 2 randomized controlled trials in Ireland and Canada [56,57], and the greater than 20% reduction in anxiety symptom scores from baseline to 6 weeks and 3 months in subscribers of Text4Hope [51,52], we hypothesize that the Wellness4Teachers email messaging program will reduce the prevalence and severity of stress, burnout, anxiety, depression, and low resilience symptoms among Zambian teachers by at least 20%*.* We also hypothesize that the Wellness4Teachers email program will improve mental health literacy scores in the teachers subscribing to the program by at least 20%. In addition, we hypothesize that the prevalence of moderate to high stress, moderate to high anxiety, moderate to high depression, burnout, and low resilience would be comparable to the prevalence of these conditions reported in other jurisdictions [81,82]. Finally, we hypothesize that demographic factors, socioeconomic factors, organizational factors, and class size will be associated with burnout and other psychological disorders in teachers [16,19-23,49,58].

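### The 4965 enrolment target divides by a maximum completion rate, so the 3% margin is at most a best case; it serves only a secondary objective, and power for the primary changes is not established

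*Protocol article*

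**What the plan says.** The Sample Size Estimation section starts from a population: "With the total teacher population in Lusaka, Livingstone, Kasama, and Solwezi of about 30,561". It sizes the baseline prevalence estimates "with 95% confidence and a 3% margin of error", which it puts at 993 completed surveys. It then inflates for non-completion. The planning rate is introduced as "Based on the maximum survey completion rate attained for the Text4Hope and Text4Mood programs in Alberta of 20" per cent, and the result is that "to achieve an estimated 993 completed surveys at baseline, it is planned to enroll at least 4965 teachers".

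The Limitations section, writing of web surveys whose links arrive by SMS, says that they "usually achieve a response rate of less than 20" per cent, and concedes that an email programme may fall short of the desired sample.

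The Study Objectives section makes baseline prevalence and its correlates secondary. The primary objective concerns improvement, and Outcomes and Measures defines the primary outcomes as changes from baseline to 6 weeks and to 3, 6 and 12 months. For these the Hypothesis section states that "we hypothesize that the Wellness4Teachers email messaging program will reduce the prevalence and severity of stress" and the other conditions by at least 20%. The article gives no sample size, power or expected number of follow-up responders for those changes.

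**The concern.** A planning rate should be the rate one expects. Here it is the highest rate seen in two named programmes, and the same article says that comparable surveys usually return less. The enrolment target thus has no allowance on the side where the authors themselves expect the error to fall, and the precision is stated as a flat 3%.

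The only calculation also supports a secondary objective. A reader who finds 993 in a section headed as the study's sample size may carry it over to the effectiveness question, where the relevant number is those who answer at baseline and again later. The Conclusions say that the results will inform policy and resource allocation, so the precision of both parts matters.

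**Working it through.** **Inputs from the article.** Population N = 30,561; 95% confidence; margin 3 points; 993 completed; 20% completion; 4965 enrolled (all Sample Size Estimation). Teacher counts by area (Study Setting). Two-sided alpha 0.05 (Statistical Analysis). Published prevalences (Introduction). **Assumed:** p = 0.5, since no planning prevalence is given; completion rates below 20%; and, for step 4, a relative 20% fall, within-person correlation φ of 0.3 to 0.5, and the follow-up response.

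**1. The stated figures.** The inflation reproduces: 993 / 0.20 = 4965.

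The 993 does not follow from the stated population. With n0 = 1.96² × 0.25 / 0.03² = 1067.1 and n = n0 / (1 + (n0 − 1)/N):
- N = 30,561: n = 1031.1, so 1032 completed, and 1032 / 0.20 = 5160 enrolled.
- N = 14,205 (Lusaka only, 10,822 + 3383): n = 992.6, so 993, an exact match.

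The 30,561 is the sum over all four areas: Livingstone 7185 + Lusaka 14,205 + Kasama 5825 + Solwezi 3346. An unstated p = 0.40 with N = 30,561 comes close (991.2, so 992), but the text gives no such value.

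**2. Margin with 4965 enrolled.** Margin = 1.96 × √(0.25/n × (30,561 − n)/30,560).

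| Completion | Completed | Margin (points) |
|---|---|---|
| 20% | 993 | 3.06 |
| 15% | 745 | 3.55 |
| 10% | 496 | 4.36 |
| 5% | 248 | 6.19 |

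**3. Enrolment needed for a 3-point margin (1032 completed).** 5160 at 20%, 6880 at 15%, 10,320 at 10%.

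**4. What can be said about the primary changes.** The number of pairs is at most the number of baseline completers. With p2 = 0.8 p1, the joint prevalence is p11 = p1p2 + φ√(p1(1 − p1)p2(1 − p2)). The discordant proportions are b = p1 − p11 and c = p2 − p11, with d = b − c and s = b + c. Power for a paired comparison of proportions is Φ[(d√n − 1.96√s) / √(s − d²)].

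Example: p1 = 0.38, φ = 0.3, n = 199. Then p11 = 0.1825, b = 0.1975, c = 0.1215, d = 0.076, s = 0.319, and power = Φ[(1.072 − 1.107)/0.560] = 0.475.

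Power over φ 0.3 to 0.5, by the share of 993 baseline completers who answer again:

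| Baseline prevalence (cited in the Introduction) | 199 pairs (20%) | 497 pairs (50%) | 993 pairs (100%) |
|---|---|---|---|
| 8.3% (lowest stress) | 11–14% | 22–29% | 39–51% |
| 25.12% (lowest burnout) | 30–39% | 62–76% | 89–97% |
| 38% (lowest anxiety in the range given) | 48–61% | 85–94% | about 99% or more |
| 67.5% (anxiety, Egypt) | 91–97% | over 99% | over 99% |
| 74% (highest burnout) | 96–99% | over 99% | over 99% |

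The answer runs from clearly too few to ample, depending on two inputs that the article does not fix.

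**The case against.** The article is open about much of this. It calls 20% a maximum, sets 4965 as a floor rather than a cap, ties 993 to prevalence estimates at baseline, and warns in Limitations that the sample may not be reached. The figure of less than 20% is stated for links sent by SMS, not email. All of this stands and softens the point. It does not remove the conflict, because the warning changes neither the target nor the stated margin, and its size is not given. Nor does the article offer any reason to expect email to do better; its caveat points the other way.

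A reader might go further and infer that the study cannot test the hypothesised 20% reduction. The documents do not support that. The low figures arise if only 20% of baseline completers answer again, and the article does not say this; people who have answered once may well respond more often. Deducting a further 15% for unsubscribing would probably count the same people twice, since unsubscribers would already be among the non-responders, and the article says less than 15%. The test used in step 4 is also not the planned one. The Statistical Analysis section uses a paired t test on mean changes, which with 199 pairs has 80% power for a standardised change of about 0.20. It adds a comparison with new subscribers that needs no pairs.

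A reader might also take 20% as the best rate ever recorded. The text limits it to two Alberta programmes.

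**Conclusion.** The point holds for the baseline precision. A flat 3% is not what 4965 enrolled should be expected to give: about 3.1 points at 20% completion, 3.5 at 15% and 4.4 at 10%, taking p = 0.5 and N = 30,561. The excess at 20% is small (0.06 points) and comes from the mismatch between 993 and the stated population. The larger loss comes from completion below the maximum, by an amount that the article does not quantify.

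For the primary changes the finding is narrower: power is not established. Whether it is adequate cannot be decided from the article, because it turns on the prevalence and on a follow-up response that is not given.

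**What to change.** 1. Replace the flat 3% with baseline margins of about 3.1, 3.5 and 4.4 points at 20%, 15% and 10% completion, marking the two lower rates as assumptions.
2. Reconcile the population with the sample size: either 1032 completed surveys for the four areas together, or a statement of which population or planning prevalence gives 993.
3. Define the recruitment target as completed baseline surveys (1032 for 3% at the stated population), monitored over the 12 enrolment months, in place of subscriptions.
4. State that 993 is not a sample size for the effectiveness objective, and give the expected precision of the paired changes over a stated range of follow-up response.

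The cost is a less favourable stated precision and a simple running count of completions. Items 1, 2 and 4 are wording. Item 3 does not by itself fix a larger number of subscriptions, but if completion runs below 20%, reaching 1032 would need more of them (step 3 of the working).
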